### Primary outcome and measures

#### Gestational weight gain

The primary outcome is the proportion of women with a gestational weight gain within IOM guidelines. A medical record review will compare the last weight recorded in pregnancy (taken at the maternity service at 36 weeks onwards and as close as practical to birth) with the woman's booking-in weight (taken at the maternity service when the woman's BMI is calculated).

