## Abstract

**Background:**

The increased prevalence of obesity in pregnant women in Australia and other developed countries is a significant public health concern. Obese women are at increased risk of serious perinatal complications and guidelines recommend weight gain restriction and additional care. There is limited evidence to support the effectiveness of dietary and physical activity lifestyle interventions in preventing adverse perinatal outcomes and new strategies need to be evaluated. The primary aim of this project is to evaluate the effect of continuity of midwifery care on restricting gestational weight gain in obese women to the recommended range. The secondary aims of the study are to assess the impact of continuity of midwifery care on: women's experience of pregnancy care; women's satisfaction with care and a range of psychological factors.

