In 2009 the American Institute of Medicine (IOM) published revised guidelines on how much weight a woman should gain during pregnancy and highlighted the importance of intervention in pregnancy to prevent *both *postpartum weight retention and childhood obesity [22]. The IOM recommends that women who are obese (BMI of 30 kg/m^2 ^and above) should gain approximately 5 to 9 kg. Excessive gestational weight gain is defined as weight gain above this recommended guideline. A recent systematic review of studies designed to prevent excessive gestational weight gain [23] revealed that, across seven studies, 63-74% of obese women gained more than 9 kg during their pregnancy and therefore exceeded the IOM guidelines for weight gain. Indeed, the adherence to recommended weight gain guidelines appears to be significantly lower for obese, as opposed to healthy weight, pregnant women [24]. There is limited evidence to support the effectiveness of dietary and physical activity lifestyle interventions in preventing adverse perinatal outcomes. In a systematic review of nine trials involving 743 women, Dodd and colleagues [25] concluded that the effectiveness of antenatal lifestyle interventions remain unclear. This is of significant concern and forms the rationale for trialling a different approach to preventing excessive weight gain in obese women.

Maternity reform at both federal [26] and state [27] levels of government promote the benefits of continuity of care and the expanded role of midwives working collaboratively in multidisciplinary teams. Continuity of care can be defined as care that is provided by the same clinician or small group of clinicians throughout pregnancy, birth and the postnatal period [28,29] and is often used in the context of models of midwifery care. There is evidence from a systematic review involving 11 trials and 12,276 women [30] that supports the beneficial effects of continuity of midwifery care on improving selected outcomes for women with no evidence of adverse outcomes. Hatem et al. propose that the underpinning philosophy of midwife-led care is normality and that caution needs to be exercised where medical complications exist and care needs a multidisciplinary approach [30].

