### Aims

This project has one primary aim: to measure the impact of continuity of midwifery care compared to routine care on restricting excessive gestational weight gain in obese women. Secondary aims are to measure the impact of continuity of midwifery care compared to routine care on obese women's experience of pregnancy care, women's satisfaction with care and selected psychological factors.

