### Power, sample size and retention

A difference between groups of 20% is deemed clinically significant. The proportion of obese women gaining weight in excess of evidence based guidelines is approximately 65% [23]. It is estimated that 107 women per study arm (total of 214 participants) is required in order to detect a difference of 20% between groups with 80% power at a 0.05 level of significance [41]. Based on current booking numbers and the prevalence of obesity at the recruitment sites, approximately 74 women will be eligible to participate each month. To accommodate an anticipated 77% participation rate [42] and a 15% attrition rate [42], the required sample will be recruited in four and a half months.

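### The primary outcome is gain within the 5 to 9 kg range, but the sample size is built on gain above that range, so 80% power is not established for the primary outcome

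*Protocol article*

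**What the plan says.** The protocol article deals with the upper limit alone in some places and with the whole range in others.

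- **Guideline (Background).** Obese women "should gain approximately 5 to 9 kg". The next sentence reads: "Excessive gestational weight gain is defined as weight gain above this recommended guideline". The Background also cites a review in which 63-74% of obese women gained more than 9 kg.
- **Primary outcome (Gestational weight gain).** "The primary outcome is the proportion of women with a gestational weight gain within IOM guidelines".
- **Analyses.** The primary comparison is a chi-square test and odds ratio on the proportion who keep gain to recommended levels.
- **Aims.** The single primary aim is "to measure the impact of continuity of midwifery care compared to routine care on restricting excessive gestational weight gain in obese women".
- **Abstract.** The primary aim is "to evaluate the effect of continuity of midwifery care on restricting gestational weight gain in obese women to the recommended range". The last paragraph of the Background words it the same way.
- **Power, sample size and retention.** "The proportion of obese women gaining weight in excess of evidence based guidelines is approximately 65" per cent. With a 20-point difference, 80% power and a 0.05 level, this leads to 107 women per arm.

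No section gives the proportion expected within 5-9 kg or the proportion expected below 5 kg. None says that gain under 5 kg counts as being within the guideline.

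**The concern.** Taken literally, a woman who gains 4 kg fails the primary outcome, yet in the sample-size calculation she belongs with the women who did not exceed the guideline. The 35% who do not exceed (100% − 65%) are the within-range and below-range women together.

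An intervention meant to restrict gain can move women from above 9 kg into the range, and can also move women out of the range at its lower end. The change in the within-range proportion can then be smaller than the change in exceedance. The trial could achieve the 65% to 45% reduction it appears to be sized for and still have a poor chance of a significant primary result.

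There is also a question of interpretation. In an unblinded trial, if the choice between ‘within range’ and ‘not above 9 kg’ stays open, there are two candidate primary results.

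**Working it through.** **Inputs from the protocol:** 65% above guideline in controls, 20-point difference, 0.05 level, 80% power, 107 per arm, range about 5 to 9 kg. **Assumed, because not given:** the share *b* of controls gaining under 5 kg (5% to 20%) and, in step 4, the SD of gain (4 to 8 kg). The test is taken as two-sided, which reproduces the stated size.

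**1. The stated sample size.** With p1 = 0.65, p2 = 0.45, mean 0.55:

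n = [1.96·√(2·0.55·0.45) + 0.842·√(0.65·0.35 + 0.45·0.55)]² / 0.20² = (1.379 + 0.580)² / 0.04 ≈ 96.

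The continuity correction, (n/4)·[1 + √(1 + 4/(n·0.20))]², gives 106, close to the stated 107. So 107 is the size for 65% versus 45% *above* the guideline. The same calculation serves 35% versus 55% *within* range only when *b* = 0. At 107 per arm, power is 80.5% with the continuity correction and about 83-84% without it.

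**2. If the 20 points applies to the within-range proportion.** The control proportion is 0.35 − *b*. Power at 107 per arm (uncorrected chi-square, exact enumeration) is 83%, 85%, 87%, 90% and 93% for *b* = 0, 5, 10, 15 and 20%. Nothing is lost on this reading.

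**3. If exceedance falls from 65% to 45% and those women divide as controls do.** The within-range gain is 20 × (0.35 − *b*)/0.35 points. For *b* = 10%, it is 20 × 0.25/0.35 = 14.3 points, so 25.0% versus 39.3%. The normal formula is

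power = Φ{[d − 1.96·√(2·p̄·(1−p̄)/107)] / √([p1(1−p1) + p2(1−p2)]/107)} = Φ[(0.1429 − 0.1252)/0.0631] = Φ(0.28) ≈ 61%.

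| Controls under 5 kg (assumed) | Within range, control vs intervention | Difference (points) | Power, uncorrected | Power, continuity-corrected | n per arm for 80%, corrected |
|---|---|---|---|---|---|
| 5% | 30.0% vs 47.1% | 17.1 | 73% | 69% | 137 |
| 10% | 25.0% vs 39.3% | 14.3 | 61% | 55% | 181 |
| 15% | 20.0% vs 31.4% | 11.4 | 49% | 42% | 246 |
| 20% | 15.0% vs 23.6% | 8.6 | 36% | 29% | 355 |

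The uncorrected column is by exact enumeration. The normal formula agrees to within a point.

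**4. If every woman’s gain shifts down by the same amount.** Let gain be normal with 65% and 45% above 9 kg. The means are then 9 + 0.385·SD and 9 − 0.126·SD.

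| SD (assumed) | Within range, control vs intervention | Power, uncorrected |
|---|---|---|
| 4 kg | 26.7% vs 35.9% | 31% |
| 5 kg | 23.2% vs 30.0% | 20% |
| 6 kg | 20.4% vs 25.6% | 15% |
| 7 kg | 18.1% vs 22.2% | 12% |
| 8 kg | 16.2% vs 19.6% | 10% |

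This is the severe end. At SD 6 kg the under-5 kg share goes from 14.6% to 29.4%, so about 15 of the 20 points pass below the range.

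**5. How much movement below 5 kg can be tolerated.** Keep 65% to 45% above 9 kg and let the under-5 kg share rise by a few points. Power is 81% for a 1-point rise from 5%, 80% for 2 points from 10%, 84% for 2 points from 15%, and 81% for 4 points from 20%. The tolerance depends on *b*. From 5%, a 2-point rise (30% versus 48%) already gives Φ[(0.18 − 0.1307)/0.0655] ≈ 77%.

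**The case against.** The strongest reply is that the protocol is more consistent than it looks. The Abstract and the end of the Background word the aim as the recommended range, and the primary outcome and the Analyses follow that wording. On this view the Aims section is the outlier, and counting a woman below 5 kg as outside the range is what the aim intends. The 20-point difference is also not expressly attached to exceedance. Set on the within-range proportion, it gives at least the stated power for every share below 5 kg examined. One could also read the outcome loosely as not exceeding the upper limit, in which case it is the exact complement of the powered quantity.

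Much of this stands. A reader might infer that the outcome contradicts the trial’s aim. The documents do not support that, because the aim is stated both ways. A reader might infer that the power is lost, or that 80% survives only if no additional women fall below 5 kg. Neither follows: steps 2 and 5 show cases where it is kept. The 10-31% figures should not be taken as an expected value either, since they rest on assumed SDs and on a uniform shift that no section supports.

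What does not stand is the idea that these readings settle the matter. The only control proportion supplied is an above-guideline rate. No section attaches the 20 points to the within-range proportion or treats gain under 5 kg as success. Nor is this a detail that a separate analysis plan would ordinarily supply, because the outcome and the power basis are both printed here and they differ.

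**Conclusion.** The point holds in this form: the stated 80% power was derived for the proportion above the guideline and is not established for the stated primary outcome, the proportion within it. The aim is worded both ways and does not decide between them.

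The size of the effect depends on a figure the protocol does not give, the share gaining under 5 kg. If 5-20% of controls do so and the women who leave the above-9 kg group divide as controls do, power is about 73% down to 36%. A uniform shift of normal gain with SD 4-8 kg would take it to 31% down to 10%. It is about 80% or more if the under-5 kg share rises by only about 1 to 4 points (how many depends on the control share), or if the 20 points was meant for the within-range proportion. The mismatch should be resolved before analysis because it determines what the primary result means.

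**What to change.** Choose one outcome before analysis and make the Abstract, the end of the Background, Aims, Gestational weight gain, Power and Analyses sections agree with it.

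- **Option 1: upper limit.** Define the primary outcome as the proportion gaining more than 9 kg. The 65%, the 20 points and 107 per arm then apply as they stand. Reword the aim in the Abstract and Background, and report the split into under 5, 5-9 and over 9 kg descriptively, so that movement below the range is visible.
- **Option 2: range.** Keep gain within 5-9 kg. Replace the 65% with an assumed within-range control proportion and a difference on that scale, give their basis, and restate the power. If the difference really is 20 points within range, 107 per arm suffices on the power target. If it is 65% to 45% exceedance with proportional movement, the requirement is about 137 to 355 per arm for 5% to 20% of controls below 5 kg. Reword the Aims section to match.

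Option 1 needs wording changes only, in the protocol and wherever the outcome is registered or repeated, with no new data and no extra women. Option 2 needs the same edits and a new power statement, and possibly more women, depending on the proportions assumed.

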### Participants

The participants will be 214 primigravid women who attend one of the recruiting maternity services for pregnancy care (Eastern Health, Barwon Health and Goulburn Valley Health) during the recruitment period and at booking have a BMI≥30 and are less than 17 weeks gestation [8]. Women will be excluded from participating in the study if they: Are unable to give informed consent in English; have a multiple pregnancy; are currently experiencing vaginal bleeding; have a severe medical condition that prevents them from being randomised to a continuity of midwifery care model or have already commenced in a shared-care model of care with their General Practitioner.

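### The primary outcome applies a whole-pregnancy weight-gain range to a shorter window that varies between women, so some are misclassified, largely alike in both arms

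*Protocol article*

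**What the plan says.** Under Gestational weight gain the protocol article states: "The primary outcome is the proportion of women with a gestational weight gain within IOM guidelines". The end weight is set as follows: "A medical record review will compare the last weight recorded in pregnancy (taken at the maternity service at 36 weeks onwards"; the full condition on its timing is "taken at the maternity service at 36 weeks onwards and as close as practical to birth". The start weight is the "booking-in weight (taken at the maternity service when the woman's BMI is calculated"). Under Participants, eligible women "at booking have a BMI≥30 and are less than 17 weeks gestation", so the start weight may be taken at any point up to that limit.

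The Background says that the Institute of Medicine (IOM) "published revised guidelines on how much weight a woman should gain during pregnancy" and gives about 5 to 9 kg for obese women. It also reports that "63-74% of obese women gained more than 9 kg during their pregnancy". The section on power and sample size takes approximately 65% exceeding the guideline from the same review. It plans 107 women per arm to detect a 20-point difference with 80% power at the 0.05 level.

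The article does not scale the limits to the observed interval, adjust for gestation at either weight, or mention a pre-pregnancy weight.

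**The concern.** The yardstick covers the whole pregnancy and the measurement covers part of it. A woman booked at 8 weeks and last weighed at 40 contributes 32 weeks of gain. One booked at 16 weeks and last weighed at 36 contributes 20. Both are held to the same 5 and 9 kg.

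If there is net gain outside the window, both limits misfire: some women who truly gained more than 9 kg are counted as within range, and some who were truly within range are counted as below it. A woman's class then depends partly on when she booked.

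At stake is the meaning of the only primary outcome. The trial aims to restrict gain to the recommended range, and a proportion computed this way does not directly show how many women achieved that. The planning rate is affected too if, as its wording suggests, it describes whole-pregnancy gain.

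This is more than a detail left to an analysis plan. The article fixes both weighing points and the range, and a pre-pregnancy weight not asked for at recruitment would be hard to recover later.

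**Working it through.** **1. The plan's own figure.** Inputs from the power section: 65% against 45% above the guideline, 80% power, alpha 0.05 (two-sided assumed, since sidedness is not stated). The mean proportion is 0.55.

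- n = [1.96·√(2·0.55·0.45) + 0.8416·√(0.65·0.35 + 0.45·0.55)]² / 0.20² = (1.379 + 0.580)² / 0.04 = 95.9, so 96 per arm.
- With continuity correction: n' = (n/4)·[1 + √(1 + 4/(n·0.20))]² = 105.7, so 106 per arm against 107 stated. The figure reproduces.

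**2. Model for misclassification.** The documents give no SD of gain and no amount of gain outside the window, so both are assumed.

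- Whole-pregnancy gain is Normal with SD s = 5 to 8 kg.
- The mean is set so that 65% exceed 9 kg: mean m = 9 + 0.385·s, which is 10.93, 11.31, 11.70 and 12.08 kg for s = 5, 6, 7 and 8.
- The same u kg falls outside the window for every woman.

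Measured gain is true gain minus u, so:

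- truly above 9 kg but counted within: Φ((9+u−m)/s) − Φ((9−m)/s)
- truly within but counted below: Φ((5+u−m)/s) − Φ((5−m)/s)

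For s = 6 and u = 1: (0.4135 − 0.3500) + (0.1880 − 0.1464) = 0.0635 + 0.0416 = 10.5%. For s = 6 and u = 2: 0.1293 + 0.0898 = 21.9%.

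| Missed | Quantity | SD 5 | SD 6 | SD 7 | SD 8 |
|---|---|---|---|---|---|
| 0 kg | within 5-9 kg | 23.2% | 20.4% | 18.1% | 16.2% |
| 1 kg | misclassified | 12.1% | 10.5% | 9.3% | 8.3% |
| 1 kg | above 9 kg | 57.4% | 58.7% | 59.6% | 60.3% |
| 1 kg | within 5-9 kg | 26.4% | 22.5% | 19.6% | 17.4% |
| 2 kg | misclassified | 25.4% | 21.9% | 19.2% | 17.1% |
| 2 kg | above 9 kg | 49.4% | 52.1% | 54.0% | 55.4% |
| 2 kg | within 5-9 kg | 29.0% | 24.3% | 20.9% | 18.4% |

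The share within 5-9 kg moves little because errors at the two limits partly cancel. Who is in that group changes much more. At SD 6, 0.0635/0.2255 = 28% of women counted within range truly exceeded 9 kg when 1 kg is missed, and 0.1293/0.2431 = 53% when 2 kg is missed.

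**3. Effect on sample size.** These figures use the scale on which the plan was powered, the share above 9 kg.

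- For a 20-point absolute difference, the continuity-corrected n is 107, 106 and 103 per arm at control rates of 60%, 55% and 50%. The planned 107 covers each.
- If the relative effect 45/65 were constant instead, n would be 125, 147 and 174 per arm. Power with 107 per arm (no continuity correction) would be 78%, 70% and 63%. The plan does not make this assumption; it specifies an absolute difference.

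**The case against.** Two measured clinic weights are a defensible choice over recalled weight. The end weight is the last one recorded, close to birth, which limits the loss at that end. The booking weight is taken before randomisation, so gestation at booking is balanced in expectation, and the Analyses section already allows multivariate analysis if baseline characteristics differ. All of this stands, and it makes the problem mainly one of non-differential misclassification.

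A reader might go further in four ways that the documents do not support:

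- **The undercount could rival the 20-point effect.** It applies to both arms, so it shifts the level and cannot be set against a between-arm difference.
- **The comparison is biased.** That would require the timing of the last weight to differ by arm. Unblinded care makes this possible, but nothing shows that it will happen.
- **The 65% is wrong.** Its wording points to whole-pregnancy gain, but the article does not give the start and end weights used in the reviewed studies. If they also began from early clinic weights, the rate may fit.
- **The sample size fails.** For the stated absolute difference it does not.

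The direction of the error also assumes net gain outside the window. Net loss before booking would misclassify women the other way.

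The objection leaves the mismatch itself in place: an unscaled whole-pregnancy range applied to windows of unequal length.

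**Conclusion.** The concern holds as a flaw in the definition of the primary outcome. As written, the rule would misclassify about 8-12% of women if 1 kg is missed and 17-25% if 2 kg is missed, and the reported proportion could not be read directly as adherence to the 5-9 kg guideline. These sizes rest on an assumed Normal distribution, an SD of 5-8 kg, 65% truly above 9 kg and a common amount missed; none of the kg figures for missed gain comes from the documents.

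On a strict reading of the outcome as 5-9 kg, the headline proportion itself moves only about 2 to 4 points at SD 6 for 1 to 2 kg missed. The damage is therefore to interpretation and precision more than to the level. Bias between arms is not shown. The control rate above 9 kg may be lower than planned on the measured scale, but that is an inference from wording.

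**What to change.** - Keep the two measured clinic weights as the basis of the primary outcome.
- Adjust the primary comparison for gestation at booking. It is needed for eligibility and is fixed before randomisation.
- Abstract gestation at the last weight in the planned record audit and report it by arm. Do not use it as a covariate in the primary model: it arises after randomisation and care may affect it.
- Pre-specify two sensitivity analyses: one classifying each woman against limits scaled to her observed interval, and one using whole-pregnancy gain from a single recalled pre-pregnancy weight item added to the recruitment questionnaire.
- State that the 65% refers to whole-pregnancy gain and may not hold for the measured window.

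The cost is two gestational ages per woman in an audit already planned, one questionnaire item and some analysis wording. The downsides are that scaling assumes a pattern of gain and needs a source beyond the 5-9 kg given in the article, and that recalled weight carries recall error. For these reasons both belong in sensitivity analyses and should not replace the primary definition.

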### Secondary outcomes and measures

#### Women's experience of care

Provision of care in line with the standards within the UK guidelines [2] will be assessed by a review of medical records. Standards include:

Evidence of commencement of folic acid supplementation

Evidence of commencement of Vitamin D supplementation

Record of BMI recorded

Evidence of anaesthetic review if BMI≥40

Evidence of thromboprophylaxis ordered antenatally

Evidence of Glucose Tolerance Testing in pregnancy

Evidence of indications for Induction of Labour

#### Women's satisfaction with care

Validated scales used in large Victorian pregnancy cross-sectional studies [28,32] will be included to measure women's satisfaction with care, engagement and sense of control. Items use 7 point scales with extreme values verbally described (1 = disagree strongly, 7 = agree strongly). Global questions summarise the concept on balance and open ended questions provided an opportunity for additional comments.

